### Secondary analysis

Similar analysis will be performed every year until 5 years to evaluate the evolution of both surgical treatments and their implication on daily living activities. Moreover, to perform a long-term follow-up to assess the survivorship of the prosthesis or secondary changes in the APL arthroplasty group.

#### Health economics

From the provider’s perspective, direct medical costs will be calculated using activity-based costing analysis [41].

From the society perspective, indirect costs will be added to the direct costs. Indirect costs will be calculated using demographics variables (age, sex, educational level, employment status, and profession). It is based on the human capital models applied to the field of health [42]. According to this approach, the remuneration in the labor market (salary) is considered a reasonable measure of labor productivity. Based on this, the salaries that the participant ceases to receive will be estimated if they leave the job due to illness, temporarily or permanently [43, 44]. The loss of work will be calculated through the gross salary per work day (adjusting for age and sex), using data from the Salary Structure Survey of the Balearic Islands.

The value of the work performed by people in a situation of reduced productivity (“presenteism”) will be calculated as part of the sensitivity analysis, taking into account an assessment of the loss of productivity estimated by the patient and adjustment made using EQ-5D-5L [45].

The effectiveness will be based on the changes between preoperative and 1-year postoperative assessments. Incremental cost-effectiveness ratios (ICER) between both interventions will be estimated 1 year after surgery.

The cost-utility analysis will be based on the Quality Adjusted Live Year (QALY) like utility measure. Spanish version of EQ-5D-5L will provide the utilities. The incremental cost-utility ratio (ICUR) will be estimated as the ratio between the costs and QALY differences [46].

The same analysis will be performed at 1, 2, and 5 years to assess the evolution of the treatment.

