**Methods:**

A randomized, blinded, parallel-group superiority clinical trial comparing trapeziectomy with abductor pollicis longus (APL) arthroplasty and prosthetic replacement with Maïa® prosthesis. Patients, 18 years old and older, with a clinical diagnosis of unilateral or bilateral TMC OA who fulfill the trial’s eligibility criteria will be invited to participate. The diagnosis will be made by experienced hand surgeons based on symptoms, clinical history, physical examination, and complementary imaging tests.

A total of 106 patients who provide informed consent will be randomly assigned to treatment with APL arthroplasty and prosthetic replacement with Maïa® prosthesis. The participants will complete different questionnaires including EuroQuol 5D-5L (EQ-5D-5L), the Quick DASH, and the Patient Rated Wrist Evaluation (PRWE) at baseline, at 6 weeks, and 3, 6, 12, 24, 36, 48, and 60 months after surgical treatment. The participants will undergo physical examination, range of motion assessment, and strength measure every appointment. The trial’s primary outcome variable is the change in the visual analog scale (VAS) from baseline to 12 months. A long-term follow-up analysis will be performed every year for 5 years to assess chronic changes and prosthesis survival rate. The costs will be calculated from the provider’s and society perspective using direct and indirect medical costs.

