### Randomization and blinding

Patients will be randomized by the senior hand surgeon ([name]), via a remote web-based randomization system (OxMar Software, *Oxford Minimization and Randomization, an open source software*) [31], which ensures a concealed allocation sequence. Randomization will be stratified by sex and group age. Each participant will be assigned a unique identification number and a unique data case report form.

The participants and the senior hand surgeon will know the assigned treatment. The participants will have the appointments and controls as in our usual clinical practice.

The main investigator will be blinded to the treatment assignment and will collect the measures in the collection notebook, except for the radiological variables because of their association with the participant’s ID. The main investigator will assess the participant before the surgeon, on the same day in a different office.

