### Follow-up and outcomes measures

Patients will complete a baseline questionnaire, which includes clinical, sociodemographic data, and potential prognostic factors.

The primary outcome measure will be the visual analog scale (VAS) determined by changes in the distance between the patient-made marks. VAS is reliable, valid, and responsive in detecting improvements associated with pain treatment [33].

Secondary outcome measures include the Quick Disabilities of Arm, Shoulder, and Hand (QUICK DASH), a short, reliable, and valid measure of physical function and symptoms related to upper-limb musculoskeletal disorders [34, 35]. Patient-Rated Wrist Evaluation (PRWE) is a widely used measure of patient-reported disability and pain related to wrist disorders [36]. The grip strength using a dynamometer [37], followed by lateral (key) and pulp-to-pulp pinch, will be recorded (both in kilograms) with a JAMAR pinch meter [38]. The goniometry measurement is determined by a change in the range of motion, as defined by the IFSSH (Atlas of Surface Anatomy and Joint Motion. International Federation of Societies for Surgery of the Hand [Internet].Illinois. Accessed 18 December 2018. < https://ifssh.info/terminology_hand_surgery.php >). The health-related quality of life questionnaire EuroQol 5-dimensions (EQ-5D-5L) is a standardized instrument for measuring generic health status [39].

Health economic outcomes include the impact of the surgery on work and other activities (including work absence and reduction in work permanence). Direct medical costs will be calculated using activity-based cost analysis. Indirect costs will be added to the direct costs, which will be calculated using the demographics variables. The remuneration (average earnings or salary) is considered a reasonable measure of labor productivity.

The main investigator will check that the questionnaires are complete. If participants choose to withdraw from the trial, they will be asked if they agree with their data being used in this study.

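### The cost-utility ratio names no baseline adjustment; regressing QALYs on baseline EQ-5D-5L utility, sex and age group would give a more precise difference at no extra data cost

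*Protocol article*

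**What the plan says.** All references are to the protocol article.

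- **Health economics, the ratio.** "The incremental cost-utility ratio (ICUR) will be estimated as the ratio between the costs and QALY differences". On the utilities: "Spanish version of EQ-5D-5L will provide the utilities". The ratio is to be produced at 1, 2 and 5 years. No model or covariate is attached to either difference.
- **Health economics, the effectiveness measure.** Just before the sentence on the cost-effectiveness ratio stands: "The effectiveness will be based on the changes between preoperative and 1-year postoperative assessments". The QALY paragraph follows separately, and the article does not say whether this sentence also governs it.
- **Health economics, costs.** "Indirect costs will be calculated using demographics variables (age, sex, educational level, employment status, and profession"). Lost work is then valued: "The loss of work will be calculated through the gross salary per work day (adjusting for age and sex"). This sets a wage rate for each person; it does not adjust the comparison between arms.
- **Abstract, Methods.** EQ-5D-5L is completed "at baseline, at 6 weeks, and 3, 6, 12, 24, 36, 48, and 60 months after surgical treatment".
- **Follow-up and outcomes measures.** "Patients will complete a baseline questionnaire, which includes clinical, sociodemographic data, and potential prognostic factors". Employment status is not listed by name here.
- **Randomization and blinding.** "Randomization will be stratified by sex and group age". Neither baseline utility nor employment is a factor.
- **Primary analysis at 1 year; Secondary analysis.** The named comparisons are chi-square, Fisher, Student's t and Mann–Whitney, with similar analyses each year. The only look at baseline balance is descriptive.

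**The concern.** A patient's QALYs are built from utilities that start at the baseline value and tend to track it afterwards. If one arm happens to start with better utility, part of that head start appears as a QALY difference that the operation did not cause. On the societal side, lost salary arises only in people with a job, so a chance difference in the number employed adds to the cost difference.

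Cost-utility is a stated secondary objective, and the Background says the implant must be clearly better to justify its added cost. The denominator of the ratio is a difference between two means. Noise in it that a covariate already on file could remove makes the ratio less stable than it need be.

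There is also an ambiguity. If the sentence on preoperative-to-1-year changes is taken to define the QALY difference, the analyst would subtract baseline. That gives a different ratio from the same data.

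**Working it through.** The article states no QALY or cost difference, so there is no figure of the plan to reproduce. The check asks how much of a baseline imbalance reaches the 1-year QALY difference, and what adjustment gains.

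**Inputs from the article.** 53 per arm with 10% loss gives 53 × 0.9 = 47.7, about 48 evaluable per arm. Utilities to 1 year are measured at 0, 6 weeks, 3, 6 and 12 months.

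**Assumptions, not in the article.** Utility SD 0.20 (range 0.15 to 0.25); correlation r of baseline with each later utility 0.2, 0.4 or 0.6; correlation among follow-up utilities 0.5; equal SDs at all visits; QALY as area under the utility curve.

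**Step 1: size of a chance imbalance.** SE = SD × √(2/48).
- SD 0.15, 0.20, 0.25 gives 0.031, 0.041, 0.051.
- The 95% range (1.96 × SE) is ±0.06, ±0.08, ±0.10.

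**Step 2: weight of the baseline value.** With 6 weeks taken as 6/52 year, the trapezoid weights are 0.058, 0.125, 0.192, 0.375 and 0.250. The direct baseline weight is (6/52)/2 = 0.058.

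**Step 3: total carry-over.** The slope of the QALY on baseline utility is 0.058 + r × (1 − 0.058), which gives 0.25, 0.43 and 0.62 for r = 0.2, 0.4 and 0.6. So 25% to 62% of an imbalance carries over. Subtracting the whole baseline value leaves slope − 1, that is −0.75, −0.57 and −0.38: the imbalance remains, with its sign reversed.

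**Step 4: precision.** Simulation with 8,000 replicates, 48 per arm, SD 0.20 and no true effect:

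| r | Shift in plain QALY difference from an imbalance of 0.08 | SE, plain | SE, baseline subtracted | SE, regression on baseline | Variance cut, regression vs plain |
|---|---|---|---|---|---|
| 0.2 | 0.020 | 0.032 | 0.043 | 0.030 | 9% |
| 0.4 | 0.035 | 0.032 | 0.035 | 0.027 | 31% |
| 0.6 | 0.050 | 0.032 | 0.025 | 0.021 | 60% |

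The mean of the plain difference was zero to within 0.0002 in every row, so there is no systematic bias to remove. Subtraction is worse than doing nothing at r = 0.2 and 0.4. Regression is best in all three rows. The last row is generous, because it lets baseline correlate with follow-up (0.6) more strongly than follow-up visits correlate with each other (0.5).

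**Step 5: employment, societal perspective only.** Under simple randomization the SE of the difference in the employed share is √(2p(1−p)/48). That is 0.094 for p = 0.3 and 0.102 for p = 0.5 (p assumed). Stratification by sex and age group will reduce this to the extent that they predict employment. I do not convert it to euros: the Discussion cites a productivity loss of EUR 5,548 but does not say whether it is per patient or per employed patient.

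**The case against.** The strongest reply is that the quoted sentence is the ordinary definition of the ratio. It does not call the differences raw, and adjusted differences would satisfy it equally well. The article condenses a longer protocol, no analysis plan is shown, and the covariates of an economic regression are often left to that plan. The unadjusted tests are named under the clinical analysis, not the economic one. All of this stands. A reader might infer that the sponsor has committed to raw differences, but the text only leaves adjustment unnamed.

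Three further inferences are tempting and not supported:

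- *That an imbalance passes into the ratio in full, or biases it.* Carry-over is partial, and randomization leaves the plain difference unbiased on average.
- *That chance differences are as large as the effects the trial will see, or would change its conclusion.* The article gives no expected QALY or cost effect to compare with.
- *That an employment imbalance is worth a known sum per patient.* The basis of the cited figure is unknown, stratification already helps, and provider-perspective costs contain no lost salary.

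That employment status is recorded at baseline is also an inference, though a close one: it is listed among the demographic variables, and demographic characteristics are part of the questionnaire completed before randomization.

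The reply does not dispose of the point. If the sentence on changes does govern the QALY, baseline is subtracted, and Step 3 shows that this over-corrects whenever the slope is below 1. Regression on baseline is the better estimator under either reading.

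**Conclusion.** The point holds as an improvement in precision and in balance given the observed baseline, not as the correction of a bias or of a misstatement. The article names no baseline adjustment for the cost and QALY differences, although baseline EQ-5D-5L and the two stratification factors are available.

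At 1 year, about 25% to 62% of a chance imbalance in utility reaches the plain QALY difference. Adjusting for baseline utility lowers the variance of that difference by about 9% to 60%. Both ranges rest on assumed correlations of 0.2 to 0.6 and an area-under-the-curve QALY; the variance range also assumes a correlation of 0.5 among follow-up utilities. The middle case is a cut of about 31%. The 2- and 5-year ratios were not calculated. The further gain from adjusting societal cost for employment is real in direction but cannot be sized from the documents.

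**What to change.** State in the analysis plan, before outcomes are compared by arm:

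1. The QALY difference is the arm coefficient from a linear regression of QALYs on arm, baseline EQ-5D-5L utility, sex and age group.
2. For the societal perspective only, the cost difference is the arm coefficient from a regression of cost on arm, baseline employment status, sex and age group.
3. The ratio at 1, 2 and 5 years is formed from the adjusted differences, with the unadjusted differences reported beside them.
4. The preoperative-to-1-year wording does not define the QALY difference.

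The sponsor should also confirm that employment status is captured on the baseline form. If an existing analysis plan already contains these rules, confirming it is enough.

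The cost is wording only. The Data collection section requires baseline measures before surgery, so missing baseline utilities should be rare, and no new data or visits are needed.

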#### Ethics

The Balearic Island Ethical Committee has approved the trial (reference number: IB4144/20. Date: July 20, 2020).

## Discussion

Trapeziometacarpal Osteoarthritis is a common condition that causes disability. The symptoms could lead to difficulties with daily living activities and reduce capacity to work, impacting quality of life and general health [3–5]. Conservative treatment could be helpful; however, if failed, surgical treatment is considered a definitive solution [4, 6].

Many surgical procedures have been described, with preferences frequently based on personal experience [4, 7, 8]. Current trends in surgical treatment suggest trapeziectomy and ligament reconstruction arthroplasty are the most popular treatments among hand surgeons [9, 11, 12].

Several reviews have been published, all of them evaluating surgical alternatives with similar results. In conclusion, neither treatment shows superiority over others. However, trapeziectomy alone demonstrated lesser complications in contrast with the rest of the alternatives. Despite the evidence showing no benefit to ligament reconstruction after trapeziectomy, 93% of American hand surgeons prefer it over other surgical procedures [47]. Wajon updated his reviews in 2009 and 2015 and showed superiority in range of motion for trapeziectomy and ligament arthroplasty [4, 6, 8]. The lack of long-term follow-up for trapeziectomy alone could be the reason for the surgeon’s preference [6, 12, 13]. Taking into account the literature, the evidence for the treatment of TMC OA is not strong enough to change the clinical practice.

The effort to maintain range of motion and improve pinch strength with lesser recovery time has been the basis for developing different implants. However, none of them have achieved wide acceptance [16, 17]. Since 1979, the popularity of ball and socket prostheses has grown due to improvements in the design and survival curve at 10 years up to 93% [19, 20]. In addition, recent studies have shown better results for range of motion, Quick Dash, pain relief, patient satisfaction, pinch strength, and recovery time [19, 20, 48]. The most common complication of the prosthesis is related to dislocation and loosening of the components that may require revision surgery of the implant. Toffoli et al. observed 5 Maïa prosthesis failures over 80 patients (5.2%) [21], Bricout et al. reported 18 surgical revisions performed out of 156 patients [49] and Martin-Ferrero estimated a survivorship for functional implants over 10 years was 93.9% [19, 20].

On the other hand, TMC OA causes frequent consultations in outpatient clinics and costs associated with loss of productivity. It leads to substantial economic consequences for the patient, the employer, and society [50].

One of the reasons for the lack of acceptance of the ball and socket prosthesis is the increased cost of the implant without demonstrated superiority over other treatments [17]. Marks et al. reported a healthcare cost of 5.770 euros and a loss of productivity cost of over 5.548 euros for trapeziectomy and ligament arthroplasty [50]. Nowadays, the prosthesis healthcare and productivity costs are unknown.

The aim of the study is to compare the effectiveness of the trapeziectomy with ligament reconstruction arthroplasty with Maïa® prosthesis. Effectiveness indicators should be the relief of pain, functional disability measured by Quick DASH and PWRE, and the improvement of quality of life with EQ-5D-5L.

Up to date, this is the first randomized study that investigates the effectiveness and cost-utility of trapeziectomy and ligament reconstruction arthroplasty and Maïa prosthesis. We expect the findings from this trial to lead to new insights into the surgical approach to TMC OA.

## Trial status

Protocol version #2, June 15, 2020. Registered at Clinicaltrials.gov, identifier: NCT04562753. Currently recruiting. The trial start date was February 2021. The approximate date the recruitment will be completed is February 2026.

## Data Availability

The final trial data set will be available to the investigators. Results and findings of the study will be released through publications in the scientific literatura and conference presentations.
